## Abstract

**Abstract:**

**Introduction:**

Malaria molecular surveillance has the potential to generate information on biological threats that compromise the effectiveness of antimalarial interventions. This study aims to streamline surveillance activities to inform the new strategic plan of the Mozambican National Malaria Control Programme (2023–2030) for malaria control and elimination.

**Methods and analyses:**

This prospective genomic surveillance study aims to generate *Plasmodium falciparum* genetic data to monitor diagnostic failures due to *pfhrp2/3* deletions and molecular markers of antimalarial drug resistance, to characterise transmission sources and to inform the implementation of new antimalarial approaches to be introduced in Mozambique (chemoprevention and child malaria vaccination). The study, to be conducted between 2024 and 2026, will use three sampling schemes: a multicluster probabilistic health facility survey in the 10 provinces of the country to detect *pfhrp2/3* deletions and markers of antimalarial drug resistance; dense sampling of all clinical cases in representative districts in the south targeted for elimination to characterise malaria importation and identify sources of transmission; and testing of pregnant women for malaria at their first antenatal care visit to assess malaria burden and molecular trends. Using a multiplex amplicon-based sequencing approach, the study will target microhaplotypes informative of genomic diversity and relatedness, as well as key drug resistance-associated genes, *pfhrp2/3* deletion and malaria vaccine targets. Key genomic information will be visualised in a dashboard integrated into the District Health Information System V.2-based Malaria Information Storage System for programmatic use.

**Ethics and dissemination:**

The protocol was reviewed and approved by the national ethics committee of Mozambique (Comité Nacional de Bioética para Saúde, Ref: 680/CNBS/23). Project results will be presented to all stakeholders using study-specific brochures and published in open-access journals.

**Trial registration number:**

NCT06529237.

STRENGTHS AND LIMITATIONS OF THIS STUDYA multicluster probabilistic health facility sampling scheme will be used to detect *pfhrp2/3* deletions and markers of antimalarial drug resistance across the 10 provinces in Mozambique.High-throughput sequencing will be used to target 165 microhaplotypes informative about *P. falciparum* genomic diversity and relatedness as well as markers associated with antimalarial drug resistance, diagnostic failure and vaccine targets.A new outbreak detector (EpiFRIenDs) will be used for outbreak monitoring and investigation of transmission sources in malaria elimination areas.Malaria incidence will be calculated considering potential biases (health-seeking behaviour, reporting and testing and alternative causes of fever) and used to compare its relationship with metrics of parasite genetic diversity.District Health Information System V.2-based genetic dashboard will be used for an easy visualisation of genomic outcomes.

## Introduction

 Mozambique is among the 10 countries with the highest malaria burden in the world, with an estimated 10.4 million cases in 2022.^1^ Malaria transmission is highly heterogeneous across the country, with a high burden in the north and a very low burden in the south, requiring different strategies for effective control and elimination.^2^ With the aim of strategically using genetic variation in *Plasmodium falciparum* to strengthen the decision-making capacity of malaria control and elimination programmes,^3^ a functional malaria molecular surveillance (MMS) system has been established in Mozambique^4^ to (1) detect the emergence of mutations conferring resistance to antimalarial drugs (ie, artemisinin-based therapies and sulfadoxine–pyrimethamine [SP] used for chemoprevention)^5^ and deletions affecting rapid diagnostic test (RDT) sensitivity (ie, *P. falciparum* histidine-rich protein 2 [*pfhrp2*])^6 7^; (2) characterise key drivers of ongoing malaria transmission with the goal of identifying transmission foci^8 9^ and differentiate between indigenous and imported cases in areas approaching elimination^10^,^12^; and (3) test the value of *P. falciparum* genetic data to recapitulate epidemiologic features of malaria transmission and inform the effectiveness of antimalarial interventions.^13^,^18^ As part of these activities, *P. falciparum* epidemiologic and genetic surveillance has also been integrated into antenatal care (ANC) clinics as a cost-effective sentinel surveillance approach.^19^,^21^

The National Malaria Control Programme (NMCP) in Mozambique is entering a new strategic cycle (2023–2030) with a plan that includes genomic surveillance to guide programmatic decisions on five key antimalarial tools (figure 1): (1) malaria diagnosis using RDTs based on histidine-rich protein 2 (HRP2); (2) treatment with artemisinin-based combination therapies (ACTs), including diversification schemes to reduce the emergence of resistance^22^; (3) chemoprevention for pregnant women (intermittent preventive treatment in pregnancy), children (perennial malaria chemoprevention [PMC] and seasonal malaria chemoprevention [SMC]) and all populations in elimination and emergency settings (mass drug administration [MDA]); (4) introduction of the R21/Matrix-M vaccine^23^; and (5) reactive interventions in very low-transmission settings. However, as in most high-burden countries, limited resources make it difficult to roll out these interventions simultaneously throughout the country. In addition, there are constantly evolving threats to the effectiveness of these interventions, including gene deletions of RDT targets,^6^ infection with non-*falciparum* species, resistance to therapeutic^24 25^ and preventive^25 26^ antimalarials, importation of infections,^27^ immune escape to malaria vaccines (R21/Matrix-M^23^ and RTS,S^28^) as well as to other immunological interventions (eg, monoclonal antibodies^29^). Thus, the overall effectiveness of the NMCP strategy will depend on the NMCP’s ability to address emerging threats, prioritise protection for those most in need and deploy tools when and where they are likely to be most effective through local decision-making.

**Figure 1 F1:**
[figure not shown]
Project expected outputs and impact. ACT, artemisinin-based combination therapy; ACT-R, Resistance to ACT; ANC, antenatal care; CSP, ciscumsporozoite protein; MMS, malaria molecular surveillance; NMCP, National Malaria Control Programme; NSP, national strategic plan; QA/QC, quality assurance/quality control; RDT, rapid diagnostic test; SP/AQ/DHAp-R, Resistance to sulfadoxine-pyrimethamine/amodiaquine/dyhidroartemisinin-piperaquine; TES, therapeutic efficacy study.

The goal of this project is to use MMS to optimise the public health benefits of the NMCP 2023–2030 strategy in Mozambique. The specific objectives are threefold. First, the project will enable real-time tracking of biological threats, including diagnostic failures due to *pfhrp2/3* deletions or non-*falciparum* infections, and assessment of molecular markers of first-line ACT resistance, supported by results from therapeutic efficacy studies (TESs). It will also characterise transmission sources at local and national levels through genetic classification of cases in low-transmission districts and identify national transmission sources and sinks. Second, the project will develop tools to guide decision-making on emerging threats to antimalarial approaches planned for use in Mozambique, including parasite resistance to chemopreventive drugs and vaccine escape^23 28^ and monitor intervention-driven changes in transmission using metrics of parasite genetic diversity.^30^ Third, the project aims to strengthen analytical and translational capacity to increase production throughput and uptake of MMS indicators to inform decision-making.

## Methods and analysis

### Study design and sample size calculations

This is a prospective genomic surveillance study of *P. falciparum* samples to be collected between 2024 and 2026 from a variety of transmission intensities and geographies in Mozambique. Sampling design and efforts will be driven by target use cases. A multicluster probabilistic health facility sampling (HFS) sampling scheme^31^ will be followed to detect *pfhrp2/3* deletions and markers of antimalarial resistance across the 10 country provinces (figure 2A). Dried blood spots will be collected from a consecutive sampling of 60 RDT-confirmed malaria clinical cases per health facility, from a systematic random sample of four health facilities per province (figure 2B and table 1). Using the DRpower tool and associated web-based *pfhrp2/3* Planner,^32^ the study power was estimated to detect the prevalence of *hrp2/3* deletions above the 5% threshold at the regional level.^33^ Assuming an intracluster correlation coefficient (ICC) of 0.05 based on historical data (https://mrc-ide.github.io/DRpower/articles/historical_analysis.html), power was estimated at 92.4% (91.9%–92.9%) in regions with three provinces (12 clusters of 60 samples) and 96.9% (96.5–97.2%) in regions with four provinces (16 clusters of 60 samples). Power remains high under the more pessimistic assumption of ICC=0.1, being 78.6% (77.8%–79.4%) and 86.3% (85.6%–87%) for regions with 3 and 4 provinces, respectively. This same design will be used to estimate the prevalence of *pfdhps* mutations at codon 540 at the province level (margin of error analysis). Assuming a mutation prevalence of 90%,^34^ prevalence will be estimated to within 4.8% margin of error for ICC=0.01 and within 7.5% margin of error for ICC 0.05^31^ (assuming lower ICC than for *pfhrp2/3* given the lower variance between clusters expected when looking at smaller geographic scale). Finally, the design will be used to detect the presence of variants of concern (VOCs), namely *pfkelch13* markers of artemisinin partial resistance and *pfdhps-*581 marker of SP resistance, at the province level (presence/absence analysis). Assuming VOCs at 1% prevalence in the population, the design has 85% power to detect VOCs if ICC=0.01 and 67% if ICC=0.05^31^.

**Figure 2 F2:**
[figure not shown]
Map of the health facilities in Mozambique included in the malaria molecular surveillance project. (A) Health facilities in Mozambique. Mozambique is divided into 154 districts and 11 provinces (for surveillance purposes, we combine Maputo Province and Maputo city, giving a total of 10 provinces): three in the South region (in blue: Gaza, Inhambane, Maputo and Maputo city), four in the Central region (in green: Manica, Sofala, Tete and Zambezia) and three in the North region (in red: Cabo Delgado, Nampula and Niassa). The map shows Malaria rapid diagnostic test (mRDT) tested and *Plasmodium falciparum* positive cases among children aged 0–5 years in 2023 (District Health Information System V.2 data). The size and colours of the circle indicate the magnitude of mRDT tested and positive cases, respectively. Total number of health facility in Mozambique: 1517 (Cabo Delgado: 115; Gaza: 139; Inhambane: 134; Manica: 114; Maputo Cidade: 32; Maputo Province: 96; Nampula: 216; Niassa: 168; Sofala: 148; Tete: 131; Zambezia: 224). (B) Health clinics selected (white dots) for the multicluster sampling approach; (C) dense sampling (Maputo Province); (D) antenatal care clinics; and (E) sentinel sites where the therapeutic efficacy studies are conducted.

**Table 1 T1:** Study provinces and districts targeted in the multi-cluster probabilistic health facility survey and antenatal care (ANC)-based sampling schemes

		Health facility (January–March 2025)		ANC		
Region	Province	District	Health facilities	District	Health facilities	Period
South	Maputo city	Kamavota	HC Mavalane			
		Kamubukwane	HC Bagamoio			
	Maputo Province	Manhica	HC Xinavane	Magude	HC Magude	January 2024–December 2025
		Matola	PH Matola		HC Motaze	January–December 2024
	Gaza	Bilene	HC Macia	Manjacaze	HC Chidenguele	January 2024–December 2025
		Chibuto	HC Mukhotwene		CHC Incadine	
		Chokwe	HC Xilembene			
		Limpopo	HC Chipenhe			
	Inhambane	Funhalouro	HC Mavume			
		Jangamo	HC Cumbana	Massinga	HC Massinga Sede	January 2024–December 2025
		Maxixe	HC A. Neto		HC Rio das Pedras	
		Panda	HC Panda			
Centre	Manica	Cid. Chimoio	HC 1 de Maio	Gondola	HC Josina Machel	January 2024–December 2025
		Gondola	HC Inchope		DH Gondola	
		Machaze	HC Sambassoca			
		Sussundenga	HC Rotanda			
	Sofala	Caia	HC Sena			
		Cid. Beira	HC Ponta Gea	Chemba	HC Mulima	January 2024–December 2025
		Gorongosa	HC Pungue		HC Chiramba	
		Nhamatanda	HC Metuchira Lomaco			
	Tete	Angónia	HC Ntsendeza	Angónia	HC Ntsendeza	September 2024–August 2025
		Chiúta	HC Manje	Chiúta	HC Manje	September 2024–August 2025
		Maravia	HC Chipera			
		Macanga	HC Gandali			
	Zambezia	Gurue	HC Cotxi	Mopeia	HC Mopeia sede	January 2024–December 2025
		Maganja da Costa	HC Nante		HC Gulamo	
		Molumbo	HC Molumbo			
		Pebane	HC 7 de Abril			
North	Nampula	Nampula	HC 25 de Setembro	Malema	HC Malema	January 2024–December 2025
		Ilha de Mocambique	HP Ampara			
		Moma	HC Chalaua			
		Nacala Porto	HC Nacala Porto			
	Niassa	Lichinga	HC Magga			
		Mandimba	HC Mandimba	Cuamba	HC Cuamba	January 2024–December 2025
		Mecanhelas	HC Muhala		HC Mepessene	
		Sanga	HC Nansinhenje		HC Titimane	
	Cabo Delgado	Balama	HC Kuekue			
		Cid. Pemba	HC Paquite	Pemba	HC Natite	September 2024–August 2025
		Montepuez	HC Mirate		HC Paquite	
		Namuno	HC Namacaca			

CidCidade (city)DHDistrict hospitalHCHealth centerHPHealth postPHProvintial hospital

A dense sampling approach, focusing on clinical cases from individuals>6 months of age, will be followed to characterise malaria importation and identify sources of transmission in representative districts in the south targeted for elimination (Magude, Matutuine and Namaacha districts in Maputo Province; figure 2C; table 2). This sampling will be implemented for 12 consecutive months, starting in April 2024 in Magude and Matutuine and in August 2024 in Namaacha. The selected areas, under the criteria of an average yearly incidence below five cases/week, include nine of the 11 health facilities in Namaacha, the 13 health facilities in Matutuine district and eight out of 10 health facilities from Magude district. Fifty samples will be collected from the four excluded health facilities in Magude (Magude sede and Motaze) and Namaacha (Mafuiane and Namaacha sede) to have a representative population of these four higher transmission areas. The total expected number of samples to be collected during 1 year is 290 in Magude, 630 in Matutuine and 550 in Namaacha.

**Table 2 T2:** Districts and health facilities in Maputo Province targeted in the dense sampling scheme

District	Health facilities	Period
Magude	HC Capitine	April 2024–April 2025
	HC Facazissa	
	HC Mapulanguene	
	HC Panjane	
	HC Chichuco	
	HC Moine	
	HC Chicutso	
	HC Mahel	
	HC Magude	April 2024 until 50 samples collected
	HC Motaze	
Matutuine	HC Catuane	April 2024–April 2025
	HC Mabilibili	
	HC Mungazine	
	HC Ponta do Ouro	
	HC Zitundo	
	HC Gueveza	
	HC Manhangane	
	HC Ndelane	
	HC Salamanga	
	HC Hindanne	
	HC Matutuine	
	HC Nsime	
	HC Santa Maria	
Namaacha	HC Changalane	August 2024–August 2025
	HC Kulula	
	HC Matsequenha	
	HC Odete Mechisso	
	HC Dibinduane	
	HC Mundavene	
	HC Wamongo	
	HC Goba	
	HC Mahelane	
	HC Mafuiane	August 2024 until 50 samples collected
	HC Namaacha	

HChealth center

Pregnant women will be tested for *P. falciparum* malaria at their first ANC visit to assess malaria trends and MMS. During the first 2 years (January 2024 to December 2025), 1–3 ANC clinics per province will be selected (figure 2D; table 1) based on the average number of monthly recruitments in each province during 2023. Approximately 1300 samples are expected per each of the 10 provinces per year. Of the 13 000 samples collected across the country per year (total 26 000), 2870 are expected to be positive for *P. falciparum* by RDT (total 5740), based on the RDT-positivity rates obtained in 2023 at each province.

Finally, targeted sampling will be conducted at sentinel health facilities (figure 2E) in the four districts (Cuamba in Niassa, Mopeia in Zambézia, Dondo in Sofala and Massinga in Inhambane) where children aged 6–59 months (n=87 children per site) with microscopically confirmed uncomplicated *P. falciparum* malaria will be recruited for a TES.

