## Discussion

Developments in genomics are driving some of today’s most groundbreaking research and surveillance approaches. However, the benefits of these tools will not be fully realised unless they are rigorously tested and deployed in an integrated manner across large geographic regions. The gap in the application and use of data and evidence generated by genomic surveillance is greater in Africa than in other parts of the world, despite a high burden of many infectious diseases, including malaria. As the archetype of a disease that primarily affects the Global South, malaria provides a unique opportunity to demonstrate how attention to equity in the deployment and use of genomics can realise its immense potential benefits for human health.

MMS activities have been designed for optimal sampling, with minimal bias and sample size to achieve appropriate statistical power for each of the use cases.^31^ The multicluster probabilistic health facility sampling (60 samples in four health facilities per province; 10 provinces) will ensure high power (>92%) at the regional level under typical ICC assumptions and good power (>78%) under pessimistic assumptions to detect *pfhrp2/3* deletions above 5%; a 5% margin of error to estimate *pfdhps*-540 prevalence at the provincial level under typical ICC assumptions and within 7.5% for pessimistic assumptions; and high power (85%) at the province level for typical ICC assumptions, although power drops (67%) for pessimistic assumptions, to detect VOCs. The collection of samples from all clinical cases (dense sampling) in representative districts in the South targeted for elimination will allow to quantify the overall impact of importation on sustaining transmission, as well as for outbreak monitoring. Finally, malaria surveillance at first ANC visits can provide information on malaria trends (including seasonal patterns to inform decisions on the introduction of interventions such as SMC) and a passive means of monitoring the impact of ongoing malaria interventions on transmission (and therefore delineate areas where cases are low because transmission has declined or where cases are low because interventions are highly effective) and sudden climatic changes on malaria burden.^20 21^ Blood samples from these pregnant women will be used for MMS to complement HFSs.^19^

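### In Magude and Namaacha the four higher-transmission facilities supply only their earliest cases, up to a quota of 50, so dense sampling there is neither complete nor year-round

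*Protocol article*

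**What the plan says.** Under Study design and sample size calculations, the protocol article plans dense sampling in Magude, Matutuine and Namaacha. "This sampling will be implemented for 12 consecutive months", from April 2024 in the first two districts and August 2024 in Namaacha. Areas were selected "under the criteria of an average yearly incidence below five cases/week". This covers nine of 11 facilities in Namaacha, all 13 in Matutuine, and "eight out of 10 health facilities from Magude district".

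For the rest, "Fifty samples will be collected from the four excluded health facilities in Magude (Magude sede and Motaze) and Namaacha (Mafuiane and Namaacha sede"), with the stated aim of representing those four areas. Table 2 gives the collection period as "April 2024 until 50 samples collected" for HC Magude and HC Motaze, and "August 2024 until 50 samples collected" for HC Mafuiane and HC Namaacha. Expected one-year totals are 290 samples in Magude, 630 in Matutuine and 550 in Namaacha.

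Other sections describe the scheme without this exception. The Abstract says that it covers every clinical case. Enrolment of participants says that every positive RDT among eligible clinical cases in the three districts is kept for molecular analysis. The Discussion says: "The collection of samples from all clinical cases (dense sampling) in representative districts" will quantify the overall contribution of importation and serve outbreak monitoring.

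**The concern.** A quota that opens in a fixed month and closes when full takes the first cases, not a sample of the year. If importation varies with season (holiday travel, peak transmission), what is learned at the four sites reflects the opening months only, while neighbouring facilities contribute all seasons. Facility type and calendar time are then partly confounded.

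The quota also reverses the facility mix: the busiest sites have most of the cases in Magude and about half in Namaacha, but supply a minority of the samples. Classifying cases as local or imported is part of the third primary endpoint (Study outcomes and analysis plan). The Figure 3 legend foresees a dashboard showing the proportion of imported cases, and the Discussion claims an overall statement on importation. A user of those outputs would take them to describe all cases in the districts.

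**Working it through.** **Inputs.** Threshold of five cases a week (yearly average), quota of 50, and district totals of 290 and 550, all from Study design and sample size calculations. Two quota facilities in each of Magude and Namaacha, none in Matutuine (Table 2). Facility incidence and seasonality are not given.

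**Consistency of the plan's totals.** The 290 and 550 cannot be reproduced without facility rates. Two facilities at five a week or more have at least 2 × 5 × 52 = 520 cases a year. That exceeds Magude's whole total and nearly equals Namaacha's, so the totals fit only with the quota applied.

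**Fraction of annual cases sampled.** One facility has at least 5 × 52 = 260 cases a year. With 50 per facility, 50/260 = 19% at most. At 10 a week, 50/520 = 10%.

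**Time to fill (50 per facility).** Weeks = 50/rate: 10 at five a week, 5 at 10, 2.5 at 20. If the rate at the start is half or a quarter of a five-a-week average, it takes 20 or 40 weeks. At 1.5 to 2 times the average, it takes 6.7 to 5 weeks.

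**Share of samples against share of cases at five a week.** Sample share = quota samples/all samples. Case share = 520/(520 + samples from the other facilities), taking those facilities as fully sampled. The text does not say whether 50 is per facility, per district or in total (the last split equally here), or whether the district totals include the quota samples.

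| Reading | Magude samples | Magude cases | Namaacha samples | Namaacha cases |
|---|---|---|---|---|
| Per facility, included | 100/290 = 34% | 520/710 = 73% | 100/550 = 18% | 520/970 = 54% |
| Per district, included | 50/290 = 17% | 520/760 = 68% | 50/550 = 9% | 520/1020 = 51% |
| In total, included | 25/290 = 9% | 520/785 = 66% | 25/550 = 5% | 520/1045 = 50% |
| Per facility, excluded | 100/390 = 26% | 520/810 = 64% | 100/650 = 15% | 520/1070 = 49% |
| Per district, excluded | 50/340 = 15% | 520/810 = 64% | 50/600 = 8% | 520/1070 = 49% |
| In total, excluded | 25/315 = 8% | 520/810 = 64% | 25/575 = 4% | 520/1070 = 49% |

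Case shares rise with the rate: at 10 a week they are 78–85% in Magude and 65–70% in Namaacha.

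**Effect on a pooled proportion.** Bias = (case share − sample share) × (importation at the other sites − importation at quota sites). On the first reading the multiplier is 0.73 − 0.34 = 0.39 in Magude and 0.54 − 0.18 = 0.35 in Namaacha. Illustration, assuming 60% imported at the other sites and 20% at quota sites:
- Magude: unweighted (190 × 0.6 + 100 × 0.2)/290 = 46%; by cases (190 × 0.6 + 520 × 0.2)/710 = 31%.
- Namaacha: unweighted (450 × 0.6 + 100 × 0.2)/550 = 53%; by cases (450 × 0.6 + 520 × 0.2)/970 = 39%.

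With equal importation in the two groups, the bias is zero.

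**The case against.** The best defence is that the four sites were never meant to be part of a census. The text calls them excluded, full collection is reserved for low-incidence areas, and the Figure 3 legend ties case classification to very low-transmission areas. A reference sample from busier neighbours is a sensible source of comparison genotypes. As a design this is defensible. It does not rescue the claims of representativeness, of all clinical cases or of all positive RDTs, which are made without that limit.

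Several stronger readings are tempting, and the documents do not support them:
- **The samples cover only a few weeks of one season.** This assumes the yearly average rate at the start. Slow starts could stretch collection to 20–40 weeks.
- **The district importation fraction is biased.** No such pooled, unweighted estimator is stated. Cases are classified individually, and a fuller protocol or analysis plan might stratify or weight.
- **The case shares are firm minima.** They depend on the reading, and Table 3 exclusions (severe malaria, recent treatment, no consent) mean the other facilities have more cases than samples, which lowers the shares.
- **Outbreak detection goes blind after the quota.** Case notification and household location visits are not said to stop. Only the genetic relatedness step would lack dense-scheme samples.

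HC Magude and HC Motaze also supply antenatal samples throughout 2024, and HC Magude through 2025 (Table 1). Genetic data from these two sites therefore continue, but from pregnant women at their first visit, not from the clinical cases to be classified.

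**Conclusion.** The point holds in limited form. At four facilities in two of the three districts, the plan collects the earliest cases up to a quota. On the 50-per-facility reading this is at most about 19% of annual cases, given that excluded facilities are at or above the five-a-week threshold. That 19% ceiling does not depend on seasonality. The sample is not assured to represent the year, and the statements in the Abstract, Enrolment of participants and Discussion contradict Table 2.

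The mismatch between case share and sample share is large under every reading tabulated. Whether it biases a reported figure depends on two things not in the document: that a pooled district proportion is reported without weights, and that importation differs between the two groups of facilities. Weighting in an analysis plan could correct the facility mix but could not recover unsampled months. Matutuine, with 630 of the 1470 expected samples, is unaffected.

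**What to change.** - **Collection.** Keep the same number of samples but spread them over the 12 months, for example every k-th stored positive RDT with k = expected annual cases/50 (about every fifth at 260 cases a year). State whether 50 is per facility, per district or in total.
- **Reporting.** Give importation separately for full-collection and quota facilities. Weight any district figure by annual facility case counts from DHIS2, which Data management already lists as study data.
- **If the quota is already filled.** Weight at facility level only, since facility-month weights are undefined for months without samples, and say that those months cannot be recovered. Limit the claims of all clinical cases, of representativeness and of within-outbreak genetic analysis to the facilities and periods actually sampled.

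**Cost.** Collection at four sites stays open for a year. The specimen is the used routine RDT (Data and sample collection), so the added burden is mainly logistic. Weighted district estimates are noticeably less precise. At five cases a week, with the total including the quota, the Kish effective size in Magude falls from 290 to (190 + 520)²/(190 + 100 × 5.2²) = 174 with 50 per facility, or (240 + 520)²/(240 + 50 × 10.4²) = 102 with 50 per district. Restricting comparisons to overlapping weeks would cost more: about 190 × 10/52 = 37 samples from Magude's eight full-collection facilities.

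### The ANC totals of 26 000 samples and 5740 positives assume 24 months in all ten provinces, but Table 1 lists Tete and Cabo Delgado for 12 months only

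*Protocol article*

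**What the plan says.** In the Protocol article, under Study design and sample size calculations, the ANC paragraph sets the window and the number of clinics: "During the first 2 years (January 2024 to December 2025), 1–3 ANC clinics per province will be selected". It then gives the yield: "Approximately 1300 samples are expected per each of the 10 provinces per year". The national figures follow: "Of the 13 000 samples collected across the country per year (total 26 000") and "2870 are expected to be positive for *P. falciparum* by RDT (total 5740"). The positives are described as "based on the RDT-positivity rates obtained in 2023 at each province", but the provincial rates are not printed.

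The paragraph cites Table 1 for the clinics. In that table:

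- Tete: both clinics (HC Ntsendeza and HC Manje) are listed for "September 2024–August 2025".
- Cabo Delgado: the Pemba entry (HC Natite, with HC Paquite on the next line) is also listed for "September 2024–August 2025".
- Maputo Province: HC Motaze is listed for "January–December 2024", while HC Magude is listed for "January 2024–December 2025".
- Gaza, Inhambane, Manica, Sofala, Zambezia, Nampula and Niassa are listed for "January 2024–December 2025".

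**The concern.** The text and the table it cites describe different amounts of sampling. The totals come from doubling one year's national figure, which is valid only if all ten provinces run for two full years. Two of the ten are scheduled for one year, and a third loses a listed clinic halfway. No later period or substitute clinic is shown for any of them.

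Two things are at stake. First, the article publishes an expected yield that its own schedule does not deliver. Second, a reader who takes two years everywhere at face value will assume that year-on-year ANC data exist in every province. In Tete and Cabo Delgado each calendar month would be observed once, so data from those provinces alone can neither compare a month with the same month a year later nor separate a before/after change from the season.

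**Working it through.** **Inputs from the ANC paragraph.** About 1300 samples per province per year; 10 provinces; 13 000 samples and 2870 positives per year; 26 000 and 5740 in total.

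**Inputs from Table 1.** 24 months in eight provinces (Maputo is counted in full at this step); 12 months in Tete and Cabo Delgado. Where a second clinic's period cell is blank, it is read as sharing the cell above and is not counted as a shorter period.

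**Step 1: reproduce the stated totals.**
- Samples: 10 × 1300 × 2 = 26 000. Matches.
- Positives: 2870 × 2 = 5740. Matches.
- Implied mean positivity: 2870 / 13 000 = 22.1%.

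The totals therefore rest on 10 × 24 = 240 province-months.

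**Step 2: apply the Table 1 periods.**
- Province-months: 8 × 24 + 2 × 12 = 216.
- Samples: 8 × 2600 + 2 × 1300 = 20 800 + 2600 = 23 400.
- Shortfall: 26 000 − 23 400 = 2600, or 10%.

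By calendar year, the two provinces contribute 4 of 12 months in 2024 and 8 of 12 in 2025:
- 2024: 8 × 1300 + 2 × 1300 × 4/12 ≈ 11 267.
- 2025: 8 × 1300 + 2 × 1300 × 8/12 ≈ 12 133.

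Neither year reaches the stated 13 000.

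**Step 3: positives.** At the mean rate, 23 400 × 2870 / 13 000 = 5166, which is 574 fewer than 5740. The rates in Tete and Cabo Delgado are not given, so a range is needed. The loss is 2600 × the assumed rate in the two provinces:

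| Assumed positivity in both provinces | Positives lost | Total positives |
|---|---|---|
| 10% | 260 | 5480 |
| 22.1% (stated mean) | 574 | 5166 |
| 30% | 780 | 4960 |
| 40% | 1040 | 4700 |

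**Step 4: HC Motaze.** No clinic volumes are given. If Motaze supplies a share s of Maputo's 1300 per year, its absence in 2025 removes 1300 × s. With s anywhere from 0 to 1, the further loss is 0 to 1300 samples and the total lies between 23 400 and 22 100. The documents do not allow a point estimate.

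**The case against.** The strongest reply is that nothing inferential rests on these totals. Every power and margin-of-error figure in the sample-size section belongs to the health facility survey. The ANC numbers are introduced as approximate and expected, so they are a forecast of yield. This stands, and it limits the weight of the point. It does not remove it: the approximation applies to the annual rate per province and does not cover two absent province-years.

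A reader might infer that the planned time-series and area-by-timepoint analyses will treat Tete and Cabo Delgado as if they had two years. The article does not say so. Under Study outcomes and analysis plan these methods are only to be considered, no list of provinces is given, and such models accept unequal observation windows. The between-years comparison by Fisher's exact test concerns resistance markers and is not tied to the ANC clinics.

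A reader might also infer that any before/after contrast in these two provinces is confounded with season, and that they must be excluded. That goes too far. Their 12 months fall wholly inside the 24 months of the other provinces, which can serve as concurrent comparators through the interaction term. Only a contrast resting on their own data is inseparable from season. Restricting Maputo to HC Magude is likewise not required, because a clinic term could handle the change.

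Finally, it is tempting to assign Motaze half of Maputo's volume. Nothing supports that share. Table 1 lists a single ANC clinic in Nampula (HC Malema), so one clinic may be expected to supply about 1300 on its own.

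**Conclusion.** The inconsistency is real and its core is firm. On the Table 1 schedule the ANC sampling is expected to give about 23 400 samples, 2600 (10%) below the stated 26 000. This rests only on the article's own rate of 1300 per province per year and on the printed periods.

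The effect on positives is indicative: about 570 fewer (about 5170 in total) if the two provinces sit at the national mean, and 260–1040 fewer if their positivity is 10–40%. The Motaze effect is an additional 0–1300 samples and cannot be narrowed.

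The documents do not settle which side is wrong. The study as a whole runs to 2026 and the ANC text refers to its first two years, but no later ANC period is listed for any clinic. The point is a correction to a stated study size and does not show that any power claim or planned analysis fails.

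**What to change.** Reconcile the ANC paragraph with Table 1.

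- **If the table is right:** restate the total as about 23 400 samples or fewer, with the expected Motaze contribution made explicit. Recompute the positives from the 2023 provincial rates, which the sponsor holds, instead of the national mean. Add one sentence saying that Tete and Cabo Delgado observe each calendar month once, so their ANC data alone cannot support a like-for-like year comparison or a before/after contrast separated from season.
- **If the totals are right:** correct the periods in Table 1 for Tete and Cabo Delgado, and show how Maputo keeps its expected volume after HC Motaze ends.

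Either route costs only wording. The first also means accepting a stated total that is 10% smaller, or somewhat more depending on Motaze. No province has to be dropped from any analysis, and no power calculation has to be redone.
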